### Endpoints

The primary endpoint is the short-term safety of the treatment. Safety evaluations will be performed on days 0, week 2, 1 month, 1.5-month, 2 month, 3 month, 4 month, 5 month, 6 month, 9 month, and 12 months after treatment. Myocardial dysfunction (e.g., contractility, diastolic dysfunction, pericarditis, pericardial effusion, myocardial ischemia, and heart failure), lung injury, and other treatment-related acute and subacute (up to 6 months after irradiation) complications greater than G3 in the Common Terminology Criteria for Adverse Events ver. 5.0 will be monitored. The secondary endpoint is the efficacy of the treatment. Cardiac function assessed by imaging, reduction of VT treatment (ATP and/or shock) by ICD, presence of dose reduction of antiarrhythmic drugs, overall survival, and patient quality of life will be measured using the 36-Item Short Form Survey and EuroQol-5D. Data collected for assessment of endpoints are as shown in
Table 1. All data are registered to Research Electronic Data Capture (REDCap) at required timing as described previously. As this is the first treatment of VT using CyberKnife in Japan, we will evaluate the safety and efficacy of the treatment in three patients. If a patient enrolled in the study is not treated after enrollment, the patient is not counted, and individual enrollment will be continued until three eligible cases are treated. The enrollment will be terminated upon accumulation of three eligible cases.

**Table 1. T1:** Timing and exams of follow up.

	Base line	Day0	Wk2	1M	1.5M	2M	3M	4M	5M	6M	9M	12M
ICD record (ATP and Shock)	○	○	○	○	○	○	○	○	○	○	○	○
Holter ECG (24hr)	○	○		○			○			○		○
Echocardiography	○			○			○			○		○
12-lead ECG	○		○	○	○	○	○	○	○	○	○	○
Blood test	○	○	○	○	○	○	○	○	○	○	○	○
Chest CT	○						○			○		○
Chest Xp	○	○		○		○		○	○		○	
Cardiac MRI	○			○								○
Myocardial scintigraphy	○			○								○
QOL check	○			○								○
Adverse event		○	○	○	○	○	○	○	○	○	○	○

ECG: electrocardiogram, ATP: anti-tachycardia pacing.

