## Protocol

### Study design and patient eligibility

This prospective, single-arm, single-center study was approved by the Nagoya University ethics committee (CRB4180004) and registered to the Japan Registry of Clinical Trials (jRCTs042230030). Patients who are refractory to at least one catheter ablation and had received one or more anti-arrhythmia drug treatment with over three episodes of VT episode with therapeutic intervention (anti-tachycardia pacing (ATP) or shock) in the last three months are considered eligible to participate in the study. Because data from Asian countries are very limited, we will first design a feasibility study at a single center. The inclusion criteria are as follows: age of ≥18 years; received antiarrhythmic drug treatment after ICD implantation; with recurrent VT after at least one catheter ablation; have experienced ≥3 VT attacks within the past three months while taking at least one antiarrhythmic drug; with VT that cannot be treated with catheter ablation; without history of cardiac irradiation; and provided written informed consent.

Meanwhile, the exclusion criteria are as follows: with heart failure requiring a left ventricular assist device; with a low probability of survival of >6 months because of factors other than VT; with contraindications for irradiation; undergoing maintenance hemodialysis or peritoneal dialysis; with organic heart disease requiring surgery; with acute coronary or heart disease requiring hospitalization; at a high risk of radiation pneumonitis (e.g. idiopathic pulmonary fibrosis); with difficult-to-control pericardial or pleural effusions; having difficulty in resting in supine for 1 h; and with other illnesses or reasons that make it difficult to perform necessary examinations or follow-up investigations, or for which the principal investigator/participating physician determines that the patient is unfit to participate in this study. The discontinuation criteria are as follows: withdraws consent, or no longer meets the eligibility criteria while on the treatment waiting list, or difficult to continue the research due to an adverse event, or Accredited Clinical Research Review Committee instructs to discontinue the research, or the principal investigator/participating physician determines that the patient is unfit to participate in this study.

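### The severity threshold attached to the primary safety endpoint is worded so that, read literally, Grade 3 toxicity falls outside it, and its scope is ambiguous

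*Protocol article*

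**What the plan says.** In the protocol article, under Endpoints, "The primary endpoint is the short-term safety of the treatment". The section then lists what will be followed: myocardial dysfunction, with several cardiac examples including pericarditis, pericardial effusion and heart failure, and then "lung injury, and other treatment-related acute and subacute (up to 6 months after irradiation) complications greater than G3". The sentence closes by saying that "complications greater than G3 in the Common Terminology Criteria for Adverse Events ver. 5.0 will be monitored".

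This is the only severity criterion in the article. The abstract mentions short-term safety without a grade. No section speaks of Grade 3 or higher, and no event limit or decision rule is attached to the endpoint.

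On size, the same section states that "we will evaluate the safety and efficacy of the treatment in three patients". Table 1 has an adverse event row ticked at every visit from day 0 to month 12, with no grade limit.

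**The concern.** Two things are unsettled in the sentence that gives the primary endpoint its content.

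- **The threshold.** A strict inequality at Grade 3 leaves Grade 3 itself out. In a study built around cardiac and lung toxicity, severe events that are not life-threatening would then not meet the stated criterion.
- **The scope.** The qualifiers in "other treatment-related acute and subacute (up to 6 months after irradiation) complications", and the grade limit that follows, may apply to the whole list or only to its last item. Two analysts could classify the same Grade 3 pericardial effusion differently.

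With three patients, a single classification moves the headline from 0/3 to 1/3. No pass/fail rule or comparator surrounds that number, so the event definition carries the whole result.

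**Working it through.** The article derives no sample size, power or event rate, so there is no figure to reproduce. The check has two parts.

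**1. The wording**

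- Literal reading: grades above 3 are Grades 4 and 5. No other statement in the article modifies this.
- Wide scope: because the last item begins with *other*, the cardiac and lung items look like members of the same class, so the grade limit covers all of them. Grade 3 cardiac and lung events fall outside.
- Narrow scope: the grade limit, the relatedness restriction and the 6-month window attach only to the last item. The named cardiac and lung toxicities then carry no grade threshold at all, and the window for them is unstated although follow-up runs to month 12.

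Neither reading yields a plain rule of Grade 3 or higher for all listed toxicities.

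**2. What the literal, wide reading could do in three patients**

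Inputs:

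- n = 3 treated patients (Endpoints section).
- a = per-patient probability that the worst event is Grade 3. Assumed: 10%, 20%, 30%.
- b = per-patient probability of a Grade 4-5 event. Assumed: 5%, with 0% and 10% as a range.
- Patients are taken as independent.

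Formulas:

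- P(0/3 on the literal threshold) = (1 − b)³
- P(0/3 on Grade 3 or greater) = (1 − a − b)³
- P(0/3 on the literal threshold although at least one patient has a Grade 3 event) = (1 − b)³ − (1 − a − b)³

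With b = 5%, (1 − 0.05)³ = 0.95³ = 0.857:

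| Grade 3 rate a | 0/3, literal | 0/3, Grade 3 or greater | 0/3 literal despite a Grade 3 event |
|---|---|---|---|
| 10% | 85.7% | 0.85³ = 61.4% | 24.3% |
| 20% | 85.7% | 0.75³ = 42.2% | 43.5% |
| 30% | 85.7% | 0.65³ = 27.5% | 58.3% |

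The last column under other assumed Grade 4-5 rates:

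| Grade 3 rate a | b = 0% | b = 10% |
|---|---|---|
| 10% | 27.1% | 21.7% |
| 20% | 48.8% | 38.6% |
| 30% | 65.7% | 51.3% |

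The size depends mostly on the assumed Grade 3 rate. The direction does not: for any Grade 3 rate above zero the last column is positive.

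For context, even a true 0/3 is weak evidence. Its one-sided 95% upper bound is 1 − 0.05^(1/3) = 63.2%. The label on the count therefore matters more than any inference drawn from it.

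**The case against.** The strongest reply is that this is loose English. Under Study design and patient eligibility, what appears to be the same criterion is given once as "with over three episodes of VT episode with therapeutic intervention" and once as "have experienced ≥3 VT attacks within the past three months while taking at least one antiarrhythmic drug", so the authors do write a strict form where they seem to mean an inclusive one. That makes Grade 3 or higher the likely intent. It does not settle the matter: eligibility also states the inclusive form, whereas the safety threshold appears only in the strict form.

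The second reply is that Grade 3 events would be captured anyway through the ungraded adverse event row in Table 1, and in three patients every event can be listed. This stands, and it limits the harm to how the primary result is defined and reported. No data would be lost.

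Third, on the narrow scope, Grade 3 cardiac and lung events stay in. That reading is possible, and on it the probabilities above would apply only to other complications. It replaces one defect with another, since the named toxicities would then have no threshold.

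A reader might infer more than the text supports:

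- *That the endpoint counts only Grade 4-5 events, or that Grade 3 was excluded on purpose.* The article says such complications will be monitored, and nothing shows an intent to exclude.
- *That the trial could be declared a success on a clean result.* No success rule is defined, so 0/3 is only a possible way of reporting.
- *That restricting to treatment-related events, or leaving the baseline adverse event cell blank, is itself an error.* The first is a recognised choice whose assessment can be left to the full protocol. The second is ordinary, because baseline imaging, ECG and blood tests are scheduled.

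**Conclusion.** Wrong as written. The only severity criterion attached to the primary safety endpoint literally covers Grades 4-5, nothing else in the article brings Grade 3 in, and it is unclear which listed toxicities the qualifiers govern.

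If the sentence is applied literally to all listed toxicities, the chance that the primary result reads 0/3 despite a Grade 3 event is 24% to 58%. This assumes Grade 3 rates of 10% to 30%, a Grade 4-5 rate of 5% and independent patients. Moving the Grade 4-5 rate between 0% and 10% widens the range to 22% to 66%. These figures illustrate and do not estimate, because the article gives no rates.

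The literal wording is certain. The practical consequence is less so, given the probable intent and the unrestricted adverse event collection.

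**What to change.** In the Endpoints section, replace the threshold by *Grade 3 or greater (CTCAE v5.0)*. State that it applies to myocardial dysfunction, lung injury and other complications up to 6 months after irradiation. In the same sentence, make plain whether the restriction to treatment-related events covers all three groups or only the last.

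The change is one sentence and should be made before results are reported. It needs no new visits or data, because adverse events are already collected at every visit after baseline. The downside is that the reported toxicity count may be higher.

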### Study plan

*Target delineation and planning*

Patients will undergo expiratory and inspiratory breath-holding and respiratory-gated contrast-enhanced computed tomography (CT) to create a stereotactic body radiotherapy (SBRT) plan. A 3D map from the electroanatomic mapping system (CARTO; Biosense-Webster, Israel) and ECG-gated CT scan will be fused to the planning CT to locate the target region and calculate the motion according to the heartbeats. The precision treatment system and CyberKnife M6 radiosurgery system (both from Accuray Inc., USA), which contain Synchrony, a respiratory compensation technology, are used to plan and deliver the planned dose.
^
11
^ Positron emission tomography/CT and contrast-enhanced magnetic resonance imaging could be used as secondary reference images. ICD leads are used for respiratory tracking. A 3-mm planning target volume (PTV) margin will be added to the target, and a dose of 25 Gy will be delivered to the PTV in a single session. The dose constraints are listed in
Table 2. The PTV margin can be varied to account for setup errors and motion uncertainty, and the PTV dose can be reduced to 20 Gy to prioritize dose constraints for organs at risk. The maximum allowable dose is 32.5 Gy.

**Table 2. T2:** Dose constraints.

Organ at risk	Max dose	Volume recommendation
trachea	20.2 Gy	V10.5 Gy < 4 cc
esophagus	15.4 Gy	V9 Gy < 5 cc
stomach	12.4 Gy	V11.2 Gy < 10 cc
aorta	25 Gy	<20 Gy preferred if possible
lung	-	V7.4 Gy < 1000 cc V7 Gy < 1500 cc
heart (exclude PTV)	25 Gy	V16 Gy < 15 cc Or D50% < 5 Gy
rib	30 Gy	V22 Gy < 1 cc
colonary artery	25 Gy	<14 Gy preferred if possible
atrium	4.4 Gy	preferred if possible
valve	10 Gy	Secondary: <25 Gy
spinal canal	8 Gy	
skin	14.4 Gy	V10 Gy < 10 cc
ICD	0.5 Gy	Does not allow the beam to pass through the ICD body

*Treatment*

The treatment as an inpatient procedure for at least 24 h after irradiation will be performed by a cardiologist and a radiation oncologist. During treatment, the ICD will be turned off, while the ECG will be carefully monitored by a cardiologist. The ICD will be turned on after completion of irradiation following an equipment check.

After treatment, a planned follow-up will be performed as described in the endpoint section.

*Quality control and quality assurance*

Monitoring will be conducted in accordance with the monitoring protocol and plan separately prescribed by the monitoring supervisor. (On-site monitoring will be conducted at least three times for each patient.) Documentation monitoring will be conducted twice during on-site monitoring, once at the beginning of the study and once at the end of the study. The audit will be conducted in accordance with the audit protocol and audit plan separately specified by the person in charge of the audit. (One system audit and one case audit will be conducted on-site.)

### Dissemination

The study is registered and is open in the Japan Registry of Clinical Trials (jRCTs042230030). The outcome of the study will be published in jRCTs.

### Study status

Participant recruitment started

## Discussion

Catheter ablation is the only curative treatment for VT and is covered by insurance in Japan. Catheter ablation allows treatment while directly searching for the origin using intracardiac electrocardiography and is undoubtedly a logical treatment method. However, because it uses Joule heating from the tip of the catheter, arrhythmias originating deep in the myocardium cannot be treated. Thus, VT requiring treatment of the deep myocardium, which is a weakness of catheter ablation, requires a different energy source than catheters, and there are great expectations for radioablation using SBRT.

Since experimental animals have shown that reducing the dose to 32 Gy or less can produce an antiarrhythmic effect in the short term without causing fibrosis,
^
12
^ this protocol was designed with an upper limit on the irradiation dose. At this point, however, there is some debate as to whether it is more effective to promote fibrosis with a higher target dose to obtain antiarrhythmic effects in the long term, and we hope that setting a maximum dose in this clinical trial will provide an answer to this part of the question.

To provide completely noninvasive treatment, treatment plans have been developed and implemented using epicardial electrocardiography at leading institutions; however, using this device in Japan is difficult because it is not approved in the country. Because catheter ablation has a smaller ablation area than radioablation, and although this narrower ablation area may be the cause of VT recurrence, there are many uncertainties, such as the long-term effect of irradiating a wider area on cardiac function.

In deference to catheter ablation, which has more long-term data than radioablation, we will change the energy to be irradiated from Joule heat to radiation dose based on the findings obtained with catheter ablation. It is highly possible that the mechanism of antiarrhythmic effect of irradiation is different from that of ablation, and furthermore, the mechanism may be different between ischemic and non-ischemic diseases. Therefore, it is essential to continue radioablation trial with prospective manners.

The facility where this study will be conducted has experience in treating >50 patients with VT with catheter ablation annually, which is a very high volume in Japan. Therefore, although this will be a single-center study, we believe that the facility is appropriate for evaluating resistance to catheter ablation. As no other treatment options are available for VT and VF, this study may serve as a guide to help clinicians in treating patients who failed to catheter ablation. Furthermore, we hope that this feasibility study will provide hope for patients who are currently under the stress of ICD activation.

### Ethical considerations

Ethics approval and consent to participate: The study was approved by the appropriate institutional ethics committee (CRB4180004) and registered to the Japan Registry of Clinical Trials (
jRCTs042230030) (registration date 06/02/2023, protocol ver. 1.2).

## Data Availability

No data are associated with this article.
